#### 9.5 Concomitant Medications and Treatments

Additional medications used to treat exacerbations of the patient's condition will be recorded on a separate bronchodilator/steroids form.. No medications are contra-indicated.

#### 9.6 Co-enrolment Guidelines

To avoid potential confounding issues, patients should not be recruited to other trials concerning the acute management of asthma. Where recruitment to another trial is considered to be appropriate and without having any detrimental effect on the Humox trial, this must first be discussed with the Chief Investigator or delegated other.

## 10 Assessments and Procedures

### 10.1 Schedule for Follow-up

Following randomisation, trial participants will be assessed at set time intervals for as long as they require oxygen and until discharge.

- i. 2, 4, 6, 8, 12 hours and then every 6 hours following start of intervention
  - a. Completion of ASS
  - b. Respiratory rate, SaO2 in air (wait 2 minutes for saturations to stabilise), Oxygen therapy (L/min)
- ii. Before discharge:
  - a. Completion by parent/guardian (and patient if appropriate) of a questionnaire assessing views on what they consider are meaningful outcome measures for studies on acute asthma
- iii. Three months following discharge, parents/guardians will be asked about respiratory symptoms since discharge using a validated respiratory symptom questionnaire. If the child is booked into an outpatient clinic approximately three months following admission, they will be given the questionnaire then. If this is not so, then a questionnaire will be sent to them by post with a stamped addressed envelope. If the questionnaire hasn't been returned within three weeks, parents will be reminded by telephone and asked if they would prefer to complete the questionnaire over the phone.

## 10.2 Procedures for Assessing Efficacy

Asthma severity will be assessed as follows:

### 10.2.1 Yung's Asthma Severity Score

Yung's asthma severity score will be assessed at regular 2hrly time intervals initially, then 4 and 6 hrly as described above. This score has been validated as a measure of asthma severity in children and has been demonstrated to be reproducible and reliable with good inter-observer agreement and correlates well with oxygen saturations and lung function. It has recently been used in a NIHR study of nebulised magnesium sulphate in the treatment of acute severe asthma (MAGNETIC).

1.Yung M. Evaluation of an asthma severity score. JPCH 1996; 32:261-264

## 10.3 Procedures for Assessing Safety

Adverse events (AEs) (see section 12.1-2) will only be reported for participants where consent has been obtained and the causal relationship to the trial treatment (oxygen or delivery equipment) has been assessed and judged by the investigator to be related to the trial treatment, which occurs from the start of randomised treatment until final study assessment. The events should be recorded on a Related Adverse Event Form, which should be transmitted to the CTU within seven days of the clinical research team becoming aware of the event.

All related AEs should be followed until satisfactory resolution or until the investigator responsible for the care of the participant deems the patient to be stable.

Follow-up information for an AE should be noted on the related AE form under the heading marked 'outcome'.

When reporting AEs the investigator responsible for the care of the participant should apply the following criteria to provide information relating to event outcomes: resolved; resolved with sequelae (specifying with additional narrative); not resolved/ongoing; ongoing at final follow-up; unknown.

There are no serious adverse events anticipated which are related to the study interventions.

## 10.4 Other Assessments

The source of data will be case report forms patient notes, prescription charts and hospital computer systems. The need for oxygen will be assessed every hour with inspired oxygen titrated to maintain the patient's saturations greater than 93%. The time taken for patients to improve based on the 'stepping down' of their nebulised therapy (i.e. changed to hourly, 2 hourly or 4 hourly nebulisers) will be recorded. ASS observations will cease when the patient no longer requires the intervention i.e. the patient no longer requires oxygen. Assessment of fitness for discharge will be at baseline, then 6 hourly until "fit for discharge" criteria are met, with each site using its own paediatric asthma pathway to assess when this has happened.

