## Study Duration:

Total study duration for each patient will be the time that individual requires oxygen in hospital because of his or her asthma. Patients will be screened at presentation to A&E and if eligible (i.e. oxygen saturations below 92%), their parents/guardian will be provided with information about the study. Treatment will then be initiated according to the BTS guidelines. Standard oxygen therapy will be administered according to local practice and three back-to-back combined salbutamol/ipratropium bromide nebulisers given. If the patient still has oxygen saturation levels <92% following this initial management (typically approximately 30 minutes after presentation to A&E, but potentially up to 90 minutes), consent to participate in the study will be sought from parents/guardians. Oxygen treatment will then be changed (or not) according to randomisation. Trial assessments for the most part will reflect those routinely performed in this patient population and will be completed at randomisation, 2, 4, 6, 8, 12 hours following randomization, and then every 6 hours for as long as the patient needs oxygen. A questionnaire determining parental views on what they consider are meaningful outcome measures for studies on acute asthma will be given to parents (and where appropriate patients) during their stay in hospital. Another questionnaire assessing respiratory symptoms will be given to participants parents/guardians at a routine follow-up outpatient clinic appointment organized by the patients clinical team three months following discharge from hospital or posted to families if no such appointment is arranged.

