### **Objectives:**

This external pilot open randomised controlled trial will generate data examining study feasibility and specifically data on accrual, adherence and outcome measure stability. Data collected will inform power calculations for a future NIHR HTA multi-centre randomised controlled trial of humidified oxygen in acute severe asthma. The aim of this subsequent definitive study will be to determine whether humidified oxygen (either heated or non-heated) is more effective than standard cold, dry oxygen therapy, in the treatment of children with severe and potentially life threatening asthma.

Thirty children with acute severe asthma will be recruited into each treatment arm (90 in total) and the following outcome measures will be examined:

- Length of time continuously spent in oxygen
- Time until treatment 'stepped down' to hourly, two-hourly and four-hourly nebulised therapy
- Differences in oxygen saturation in air at set time points after entry into the study
- Changes in *Yung's Asthma Severity Score*
- Number of Salbutamol and Ipratropium Bromide nebules required by each patient following randomisation
- Requirement for escalation of treatment (i.e. need for intravenous salbutamol/aminophylline or HDU/PICU)
- Adverse events/tolerability
- Length of stay in hospital

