### 11.4 Analysis Plan

To ensure that the enrolled sample is representative of the target population demographic and clinical data will be initially described using summary statistics, means, medians, standard deviations etc, as appropriate. To determine the balance of the treatment/control groups, in terms of demographic and clinical variables, standard hypothesis tests and analysis of variance will be undertaken. As this is a pilot study and consequently not powered to detect a significant difference between groups in the main

outcome measures, no formal hypothesis tests or interim analysis are planned. The main outcome measures will be presented using summary statistics and, as an aid to identifying potential outcome measures for a definitive trial, the proportion of missing values will be assessed. To assess the feasibility of undertaking a definitive trial accrual and drop-out rates will be assessed using proportions and graphical representations.

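### Yung score recording stops when oxygen stops, so score summaries after the first hours cover only unrecovered children; Sections 1, 10.1 and 10.4 should be reconciled

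*Protocol*

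**What the plan says.** Three places in the protocol set how long children are assessed.

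- Section 10.4 names the Yung score (ASS) only: "ASS observations will cease when the patient no longer requires the intervention i.e. the patient no longer requires oxygen".
- Section 1, Study Duration, places trial assessments at randomisation and then at "2, 4, 6, 8, 12 hours following randomization, and then every 6 hours for as long as the patient needs oxygen".
- Section 10.1 says that "trial participants will be assessed at set time intervals for as long as they require oxygen and until discharge". Its item i gives the times as "2, 4, 6, 8, 12 hours and then every 6 hours following start of intervention" and lists the score, respiratory rate, saturation in air and oxygen flow.

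Change in the Yung score and saturation in air at set times are among the outcomes in Sections 1 and 2.2. So is the variable that triggers the stop: "Length of time continuously spent in oxygen" is first on the list in Section 1. Section 11.4 plans summary statistics for the main outcomes with no formal tests of them. It adds, as a help in choosing outcomes for the definitive trial, that "the proportion of missing values will be assessed". Section 11.2 also uses missing data in that choice.

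**The concern.** A child leaves the score series because he or she has recovered enough to come off oxygen. Faster recovery is what the treatments are meant to produce, so the stop rule depends on a post-randomisation outcome. Section 10.2.1 itself says that the score tracks oxygen saturation closely, and saturation decides the need for oxygen.

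At each later time point the summary in each arm then describes the children not yet recovered. A better arm loses more children from its mean, and those who remain are sicker than that arm's average. The arms compared are no longer the groups that were randomised.

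The pilot tests nothing formally. The cost falls on its stated purpose, which is to supply data for power calculations and to help choose the outcome for the definitive trial. Scores that were never recorded cannot be recovered by any analysis plan.

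**Working it through.** **1. The passages side by side, for a child off oxygen but still in hospital**

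| Place | Yung score | Saturation in air |
|---|---|---|
| Section 10.4 | stops | not mentioned |
| Section 1, Study Duration | stops, at least in the 6-hourly phase | same |
| Section 10.1 | continues, if the discharge limit governs item i | same |

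Sites could collect different data under the same protocol.

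**2. What is summarised.** Let S(t) be severity at hour t and T the time in oxygen. The randomised comparison needs the mean of S(t) over all children in each arm. The stop rule gives the mean of S(t) among children with T > t. If treatment shortens T, that condition selects differently in each arm.

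**3. How many children remain.** The protocol's only sample figure is 30 per arm (3 × 30 = 90, which agrees). It gives no distribution for T. Assuming an exponential T with median m, the number still scored is n(t) = 30 × 2^(−t/m).

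| Assumed median m | 12 h | 24 h |
|---|---|---|
| 8 h | 10.6 | 3.8 |
| 12 h | 15.0 | 7.5 |
| 24 h | 21.2 | 15.0 |

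**4. How much of a difference survives.** Illustrative model, every value assumed:

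- S(t) = max(0, S0 − k·t), with S0 normal, mean 3 and SD 1.
- k is lognormal, median 0.2 SD per hour, log-SD 0.6.
- Oxygen stops at S = 1, which gives a median time in oxygen of 9.3 h in the reference arm.
- In the faster arm k is multiplied by 1.3 or 1.5. There are 400,000 simulated children per arm.

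| Time, speed | All children | Still on oxygen | Share retained | Still scored (reference / faster) |
|---|---|---|---|---|
| 2 h, 1.5 | 0.23 | 0.14 | 61% | 93% / 88% |
| 8 h, 1.5 | 1.34 − 0.86 = 0.48 | 2.14 − 1.99 = 0.15 | 31% | 57% / 37% |
| 12 h, 1.5 | 0.86 − 0.45 = 0.41 | 2.00 − 1.87 = 0.13 | 32% | 37% / 20% |
| 8 h, 1.3 | 1.34 − 1.03 = 0.31 | 2.14 − 2.04 = 0.10 | 32% | 57% / 44% |
| 12 h, 1.3 | 0.859 − 0.581 = 0.278 | 1.996 − 1.912 = 0.084 | 30% | 37% / 25% |

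Spread is affected too. At 8 h the reference-arm SD in this model is 1.12 over all children and 0.80 among those still on oxygen.

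**5. Sensitivity.** The floor at zero matters. Without it the same linear decline retains about 15% at 8 h and 9% at 12 h. An exponential decline retains 34% to 35% at those times. A second model lets score and oxygen need differ (correlation weight 0.5 to 1.0) with recovery 1.25, 1.5 or 2 times faster. It retains 16% to 41% at 12 h and 6% to 23% at 24 h. At 12 h it leaves 9 to 14 of 30 children scored in the slower arm and 4 to 11 of 30 in the faster. The difference shrinks in every scenario; the amount depends on the model.

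**The case against.** Several points on the other side are sound.

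- **The contradiction is an ambiguity.** A reader might infer that Section 10.1 plainly orders scoring until discharge. Its sentence names both the end of oxygen and discharge, and it introduces a list that includes a questionnaire before discharge. Scoring while on oxygen, followed by the discharge items, is a coherent reading, and Section 1 leans that way. The three sections still need reconciling.
- **Section 10.4 does not stop saturation in air.** Its clause names the score alone. A stop for saturation rests on Section 1, where "and then every 6 hours for as long as the patient needs oxygen" may limit only the 6-hourly phase. The point is firm for the score and conditional for saturation.
- **The treatment effect is not lost to the trial.** Time in oxygen, step-down, nebules used, escalation and length of stay do not depend on the stop rule, and they capture faster recovery.
- **Missing data.** One might infer that the score will be marked down as an outcome because of the protocol's own rule. The documents do not show this. Section 14.2.1 requires missing data to be explained, gives a not-assessed box for each score domain at each time point, and separates items not done from items not applicable. Section 11.2's outcome list omits saturation in air altogether. What stands is that no text says which code a score takes once oxygen has stopped.
- **Early time points suffer less.** At 2 h about nine in ten children are still scored in the illustrative model, although roughly 40% of the difference is already lost there.

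**Conclusion.** The point holds for the Yung score. Under Section 10.4, score summaries after the first hours describe the unrecovered children in each arm. Contrasts between arms are attenuated, and means and SDs taken from them would misinform the definitive trial's planning. It extends to saturation in air only if Section 1 is read as ending that measurement with oxygen.

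The direction is robust. The size is not known from the protocol. A loss of about two thirds at 8 to 12 h belongs to a floored linear model with 30% to 50% faster recovery, and other assumed shapes give more or somewhat less.

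The documents do not support saying that the rule conceals the treatment effect altogether, or that all comparisons in the pilot are compromised. Severity is moderate: this is a pilot without formal outcome tests, but the lost observations cannot be recovered afterwards.

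**What to change.** 1. Reconcile Section 1 (Study Duration), Section 10.1 and Section 10.4 so that the score and saturation in air are recorded at 2, 4, 6, 8 and 12 h and then 6-hourly in every child still in hospital, on or off oxygen.
2. Record children who have gone home as discharged, not as missing, and leave them out of the missing-value proportion used in Sections 11.2 and 11.4.
3. Report the numbers on oxygen, off oxygen and discharged at each time point in each arm.
4. Because discharge also depends on recovery, step 1 alone only moves the cut-off later. Either base between-arm score summaries on the early time points when nearly all children are still in hospital, or give discharged children a best-category or rank value stated in advance.

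The cost is a wording amendment and a few extra bedside scores per child. Section 10.4 already has fitness for discharge checked 6-hourly, so some of these scores can be taken at contacts that occur anyway. The change concerns data collection only and leaves treatment as it is. It should be made before recruitment, or as early in recruitment as possible.

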## 11 Statistical Considerations

### 11.1 Method of Randomisation

The randomisation code list will be generated by a statistician (who is not involved with the HUMOX study) at the MC CTU. Participants will be randomised using two sets of randomisation envelopes, (one set for 2-5 year old children, and the other for 6-16 year olds). Participants will be randomised to warm humidified, cold humidified or cold dry oxygen in a ration 1:1:1.

### 11.2 Outcome Measures Prioritisation and Consensus

The following outcome measures will be examined in this study:

- Length of time in oxygen
- Time until treatment 'stepped down' to hourly, two-hourly and four-hourly nebulised therapy
- Yung's asthma severity score
- Number of Salbutamol and Ipratropium Bromide nebulas required by each patient
- Requirement for escalation of treatment (i.e intravenous Salbutamol/Aminophylline or HDU/PICU)
- Adverse events/tolerability
- Length of stay in hospital

These outcomes have been identified as relevant and important in a previous exercise involving consumers and paediatricians (MCRN Respiratory and General Paediatrics Clinical Studies Groups), however their relative importance has not been assessed. A consensus exercise will be undertaken to establish which outcome(s) will be taken forward to the definitive randomised controlled trial. This will involve: (1) trial participants/families (research nurses will give a one-page questionnaire to parents/guardian once the patient has become stable and has come out of oxygen), (2) lay members of the study Steering Group, (3) the MC Young Person's Advisory Group, (4) Asthma UK, (5) MC Respiratory and General Paediatric Clinical Studies Groups.

In addition, outcome measure stability, feasibility of data collection and missing data events from the pilot study will contribute to selection of the most appropriate outcome(s) based on both consensus and feasibility.

### 11.3 Sample size

This is an external pilot RCT. A pragmatic sample size of 30 in each intervention arm has been set following statistical advice.

### 11.4 Analysis Plan

To ensure that the enrolled sample is representative of the target population demographic and clinical data will be initially described using summary statistics, means, medians, standard deviations etc, as appropriate. To determine the balance of the treatment/control groups, in terms of demographic and clinical variables, standard hypothesis tests and analysis of variance will be undertaken. As this is a pilot study and consequently not powered to detect a significant difference between groups in the main

outcome measures, no formal hypothesis tests or interim analysis are planned. The main outcome measures will be presented using summary statistics and, as an aid to identifying potential outcome measures for a definitive trial, the proportion of missing values will be assessed. To assess the feasibility of undertaking a definitive trial accrual and drop-out rates will be assessed using proportions and graphical representations.

## 12 Safety

### 12.1 Terms and Conditions

#### **Adverse Event (AE)**

Any untoward medical occurrence in a subject to whom a medicinal product has been administered, including occurrences which are not necessarily caused by or related to that product.

#### **Serious Adverse Event (SAE)**

Any adverse event, that:

- results in death
- is life-threatening\* (subject at immediate risk of death)
- requires in-patient hospitalisation or prolongation of existing hospitalisation\*\*
- results in persistent or significant disability or incapacity, or
- consists of a congenital anomaly or birth defect
- is an other important medical event that may jeopardise the subject\*\*\*

\*‘life-threatening’ in the definition of ‘serious’ refers to an event in which the patient was at risk of death at the time of the event; it does not refer to an event which hypothetically might have caused death if it were more severe.

\*\*Hospitalisation is defined as an inpatient admission, regardless of length of stay, even if the hospitalisation is a precautionary measure for continued observation. Hospitalisations for a pre-existing condition, including elective procedures that have not worsened, do not constitute an SAE.

\*\*\*Other important medical events that may not result in death, be life-threatening, or require hospitalisation may be considered a serious adverse event/experience when, based upon appropriate medical judgment, they may jeopardise the subject and may require medical or surgical intervention to prevent one of the outcomes listed in this definition.

### 12.2 Notes on Adverse Event Inclusions and Exclusions

Only related and unexpected adverse events/ severe adverse events will be reported. For the purposes of this study, a related event is one related to the intervention/therapy, not the underlying condition itself. For related and unexpected events:

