#### 12.2.1 Include

- Failure to tolerate oxygen therapy e.g. failing to tolerate face mask, heated humidity/facial sore
- Nose bleeds
- Incorrect set-up of equipment/equipment failure.

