#### 12.2.2 Do not include

- Medical or surgical procedures
- Pre-existing disease or conditions present before treatment that do not worsen
- Situations where an untoward medical occurrence has occurred
- The disease being treated or associated symptoms/signs unless more severe than that expected for the patient's condition
- Changes in the amount of oxygen administered immediately following change in route of oxygen administration

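### Conflicting adverse-event rules in Sections 10.3 and 12.2 leave the listed tolerability outcome open to uneven capture between sites and to unblinded attribution

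*Protocol*

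**What the plan says.** "Adverse events/tolerability" is one of the outcomes in the Protocol Summary (Objectives), and it appears again in Sections 2.2 and 11.2.

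Section 10.3 limits reporting to events whose causal relationship "has been assessed and judged by the investigator to be related to the trial treatment". It continues: "The events should be recorded on a Related Adverse Event Form", and "All related AEs should be followed until satisfactory resolution". It refers the reader to Sections 12.1 and 12.2 but sets no expectedness condition of its own.

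Section 12.2 adds one: "Only related and unexpected adverse events/ severe adverse events will be reported". The protocol neither defines nor lists expected events.

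Under that heading, Section 12.2.1 names what to include: "Failure to tolerate oxygen therapy e.g. failing to tolerate face mask, heated humidity/facial sore", then nose bleeds and faulty or wrongly assembled equipment. Section 12.2.2 lists what to leave out, including "Situations where an untoward medical occurrence has occurred".

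The trial is open (Section 5). Section 9.4 says that whoever gives the treatment cannot be blinded, and no blinded assessment of relatedness is described.

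**The concern.** A site that follows Section 10.3 and a site that follows the opening of Section 12.2 would be working to different inclusion rules, and both could claim to have followed the protocol. Because the same reports supply a listed outcome, the inconsistency affects more than safety administration.

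Two things are at stake. First, Section 11.2 makes feasibility of data collection and missing data part of the basis for choosing outcomes for the definitive trial, and Section 11.4 assesses the proportion of missing values. With a form that is completed only when an event passes a filter, an absent form can mean that no event occurred, that the event was judged unrelated, that it was thought expected, or that nobody recorded it. Missingness for this outcome then cannot be assessed, and no later analysis can recover it.

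Second, the filter includes a causality opinion from someone who knows the allocation. If that opinion is formed differently by arm, reported tolerability will differ between arms even where the true rates do not.

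**Working it through.** **Text comparison.** Take one child with a nose bleed that the investigator considers related to the oxygen.

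| Protocol section | Rule | Reported? |
|---|---|---|
| 10.3 | Related, no expectedness condition | Yes |
| 12.2, opening sentence | Related and unexpected, 'expected' undefined | Depends on the site's view of what is expected |
| 12.2.1 | Nose bleeds named for inclusion | Yes |
| 12.2.2, third item, read with 12.1 | Leaves out any untoward occurrence | No, if taken literally |

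Section 12.1 defines an adverse event as any untoward medical event, whether or not caused by the product. The third item in Section 12.2.2 removes the same thing, so taken literally it empties the category.

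Section 12.2 also writes 'severe' where Section 12.1 defines 'serious'. The two words are not interchangeable, and Section 14.5 has the Trial Management Group reviewing SAEs.

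**Other sources of tolerability data.** The scheduled assessments in Section 10.1 collect the severity score, respiratory rate, saturation in air and oxygen flow, with no tolerability item. Section 13.2 asks for the reason when alternative treatment is given, and Section 7 requires a withdrawal CRF. Neither captures a child who has an event and stays on the allocated oxygen.

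**Illustration of the attribution filter.** There is no figure in the plan to reproduce: the protocol gives no event rate and no attribution rate. The only number used from it is 30 per arm (Section 11.3); 3 × 30 = 90 agrees with the Protocol Summary.

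Inputs:
- n = 30 per arm (protocol).
- p = true proportion of children with an event, the same in both arms (assumed: 10%, 20%, 30%).
- a = probability that an event is judged related (assumed: 0.9 in arm A; 0.7, 0.5 or 0.3 in arm B).

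Expected reported events = n × p × a. Apparent difference = p × (a_A − a_B). Apparent ratio = a_A / a_B.

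| p | a_B | Reported, A | Reported, B | Difference (points) | Ratio |
|---|---|---|---|---|---|
| 10% | 0.7 | 2.7 | 2.1 | 2 | 1.29 |
| 10% | 0.5 | 2.7 | 1.5 | 4 | 1.8 |
| 10% | 0.3 | 2.7 | 0.9 | 6 | 3.0 |
| 20% | 0.7 | 5.4 | 4.2 | 4 | 1.29 |
| 20% | 0.5 | 5.4 | 3.0 | 8 | 1.8 |
| 20% | 0.3 | 5.4 | 1.8 | 12 | 3.0 |
| 30% | 0.7 | 8.1 | 6.3 | 6 | 1.29 |
| 30% | 0.5 | 8.1 | 4.5 | 12 | 1.8 |
| 30% | 0.3 | 8.1 | 2.7 | 18 | 3.0 |

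With equal attribution the ratio stays at 1 and only the counts fall. If arms A and B change places, the ratio runs from 0.7/0.9 = 0.78 down to 0.3/0.9 = 0.33. The calculation shows how the distortion would work. It does not show which way it goes or that it will occur.

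For scale, at p = 20% and a_B = 0.5 the reported rates are 18% and 10%. The standard error of that difference is √(0.18 × 0.82/30 + 0.10 × 0.90/30) = √0.00792 = 0.089, about 9 points, so the 8-point gap is smaller than one standard error.

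**The case against.** The opposing case has five parts, and much of it stands.

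- **The inclusion list tells sites what to report.** Section 12.2 leads directly into Section 12.2.1. A reader might infer that the named events count as expected because they are listed, and so would go unreported altogether, giving zero rates in every arm. The protocol does not say that, and the list directs sites to report them. The wording is contradictory, but it does not make these events disappear.
- **Most listed events leave little room for attribution.** Section 10.3 counts the delivery equipment as trial treatment. Mask or humidity intolerance and equipment faults are related almost by definition. Real discretion remains mainly for nose bleeds, so the attribution figures above should not be applied to the whole list.
- **The direction of bias is unknown.** A reader might suppose that events on a new heated device are more readily blamed on the treatment than events on familiar dry oxygen. Section 2.1 argues that dry gas damages airway epithelium, which could push attribution the other way, and Section 3.1 says all three methods are in routine ward use.
- **No inference is planned.** Section 11.4 provides summary statistics and no formal tests.
- **Limiting safety reporting to related events is a legitimate choice** in a trial that is not a CTIMP (Section 14). That is correct for safety reporting. It does not answer the point that the same filtered reports serve as an outcome.

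The CRF is not among the documents, so it may already hold tolerability items. The protocol does not mention any.

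**Conclusion.** The inconsistency is established from the text and needs no assumptions. Section 10.3 and Section 12.2 define different reporting sets, expectedness is undefined, and one exclusion in Section 12.2.2 cancels the definition in Section 12.1. Sites could report different events for a listed outcome.

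The attribution problem is a risk of bias and not a demonstrated one. It rests on attribution differing by arm, which the documents neither show nor rule out. On the assumed inputs the apparent risk ratio is about 1.3 to 3.0 and the apparent difference 2 to 18 points, in either direction and in descriptive summaries only.

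A reader might conclude that the arms will be compared on attribution rather than on events. The documents do not support that: reported counts reflect both occurrence and judgement, and for most of the listed events the judgement is close to automatic.

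The sponsor should make the change, because it is cheap and it determines what data exist for a candidate outcome of the definitive trial.

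**What to change.** 1. In Section 12.2, delete the words 'and unexpected' so that the rule matches Section 10.3, and replace 'severe' with 'serious'. Possible wording: *Adverse events and serious adverse events judged related to the oxygen or its delivery equipment will be reported.*
2. In Section 12.2.2, correct or remove the third item. A missing 'not' is one possible explanation, and the sponsor should confirm what was meant.
3. For the tolerability outcome, record the Section 12.2.1 events as yes/no items at the assessments already scheduled in Section 10.1, in all three arms and regardless of judged cause: intolerance of the allocated delivery method, facial sore, nose bleed, equipment fault. Wording the first item around the delivery method, and not around heat, lets it apply in every arm. Tabulate these items by arm as the outcome.
4. Keep the relatedness judgement of Section 10.3 for safety reporting.

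The cost is a wording amendment and slightly more data entry at each assessment. If the CRF already holds such items, the third step only needs a sentence in the protocol. No treatment or clinical rule changes.
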